### **6.4 Pharmacokinetic data analysis**

A limited sampling strategy has been devised based on empirical/noncompartmental and model-based approaches. This approach evaluates the family of single point and paired concentrations (observed and interpolated) in order to define the minimal sampling scheme to yield adequate prediction of drug exposure (plasma AUC). A regression-based approach will be utilized using various discrete concentration permutations as predictors and AUC as the response. Based on the availability of a suitable structural model, these results will be validated with a model-based approach based on D-optimal design theory once preliminary data from the Phase I study is available. All modeling and simulations will be performed using the NONMEM software (Version V, Level 1.1, Globomax LLC; Hanover, MD).

Population PK model parameters (fixed and random) will be estimated via nonlinear mixed-effects modeling using NONMEM. An appropriate compartmental model/structure model will be developed for silymarin isomers based on the PK data collected in this study. Data from the Phase I study may be added to improve model stability. The effects of clinical and demographic factors, including but not limited to weight, height, body surface area, body mass index, ALT, age, and gender on PK model parameters will be investigated using a backward stepwise elimination procedure in NONMEM.

Individual predicted PK parameter estimates based on the final model will be used to explore the relationship between various PK metrics and clinical outcomes. Using a logistic regression, the probability of positive (or negative) outcomes will be predicted based on various PK metric expressions (i.e. Cmax, AUC).

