### **Rationale for Subject Population**

Patients with NASH will be enrolled and subsequently stratified by diabetes status. The majority of non-diabetic patients with NASH are expected to be overweight. Obesity and diabetes are the natural targets for study, given their ubiquity in the U.S. population and known association with NASH. Given the role of oxidative injury in the mechanism of NASH, silymarin's antioxidant properties would be a rationale for this approach to therapy.

The study population will exclude cirrhotic patients for several reasons. First, the histology of cirrhotics with suspected NASH often does not reflect the typical features of steatosis and steatohepatitis. Therefore, the diagnosis of NASH induced cirrhosis would be based on circumstantial evidence, such as the history of insulin resistance or obesity. Such assumptions of disease causation without histological confirmation would allow for potential misclassification

bias. Moreover, the primary endpoint of histological improvement could not be assessed in this population. Furthermore, people with cirrhosis demonstrate pharmacokinetics which differ from people without cirrhosis.

In the setting of a clinical trial, the safety of higher doses must be assessed, with a careful observation of the occurrence of clinical and laboratory adverse events. Doses of up to 1260 mg/day for up to 6 months were well tolerated in a small number of hepatitis C patients. While silymarin appears to be extremely safe, the increase in dose could be associated with unexpected adverse effects. Additionally, there may be off targets of silibinin that could cause adverse drug reactions. Silymarin or silibinin have been implicated to have inhibitory effects on cytochrome (CYP) P450 enzymes in some, but not all *in vitro* studies. However, the inhibition profile of silibinin is theoretically relevant only for CYP 3A4 and 2C9, and then perhaps only in bile, which has drug concentration 100 times that seen in serum. Examination of enzyme inhibition in human clinical trials has been reassuring, with no evidence of altered metabolism of probe drugs specific to CYP 1A2, 2D6, 2E1 or 3A4 and of non-specific probes when doses of 210-480 mg/day were administered. Silymarin does not appear to induce CYP 3A.

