## Dose Selection

As stated in the Phase I protocol, decisions regarding dose selection for the Phase II trial are primarily based upon consideration of safety and PK relationships observed for the sum of parent (i.e. "Free") silymarin flavonolignan concentrations (i.e.  $\sum$  Free silymarin). However, an unexpected finding from the Phase I study was that  $\sum$  Free silymarin accounted for only 1.7% to 7.2% of the Total concentrations of silymarin flavonolignans found in the blood for NAFLD subjects receiving 280 to 560 mg silymarin three times daily (Appendix 1, Summary Table 4). The remaining flavonolignan species that contribute to Total concentrations consist of glucuronide and sulfate conjugates (i.e. metabolites) of the parent flavonolignans. Since parent ("Free") silymarin flavonolignans undergo extensive first-pass phase 2 metabolism to glucuronide and sulfate conjugates in the GI tract and in the liver, use of  $\sum$  Free silymarin concentrations to assess drug exposures will be imprecise since it does not represent the total

amount of drug entering the body. In addition, since conjugate concentrations in blood are approximately 11.5-times greater than “Free” concentrations, a small reduction in the extent of silymarin’s metabolism to conjugates would be expected to greatly influence “Free” blood concentrations without changing “Total” blood concentrations or  $\Sigma$  Total silymarin exposures. In addition, small changes in the extent of conjugation are not easily detected in “Total” concentrations because of the high %CV in these measures.

Therefore, “Total” flavonolignan concentration, which represents all species of a flavonolignan in blood, is the best measure of the amount of a flavonolignan entering the body following an oral dose. Because any or all of the silymarin flavonolignans may contribute partially or fully to the pharmacological activity of silymarin,  $\Sigma$  silymarin concentration, which represents the sum of the concentrations of all six major silymarin flavonolignans, is the best measure of silymarin exposure for assessment of safety and efficacy endpoints. Given these considerations, mean  $\Sigma$  Total silymarin AUC was chosen for the assessment of dose-exposure proportionality in the Phase I trial and provides the basis for the selection of 420 mg and 700 mg doses administered three times daily in this Phase II study.

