##### Non-Linear Pharmacokinetics of $\Sigma$ Free silymarin plasma concentrations

“Free” parent flavonolignan concentrations can be expected to have influences on the efficacy and safety of silymarin that must be considered independent from those associated with “Total” silymarin flavonolignan concentrations. Non-linear pharmacokinetics was observed for  $[\Sigma]$  Free silymarin exposures in NAFLD subjects since a 2-fold increase in dose from 280 mg to 560 mg resulted in a 9-fold increase in the  $\Sigma$  Free silymarin AUC (see Appendix 1, Summary Table 2).  $\Sigma$  Free silymarin peak concentrations increased ~4-fold and ranged from 0.50 to 1.77 ug/ml at a dose of 560 mg in NAFLD subjects (Appendix 1, Table 15). At a dose of 560 mg, mean  $\Sigma$  Free silymarin exposures for NAFLD patients (4387 ng\*hr/ml) were 4-fold greater than those for HCV patients (1025 ng\*hr/ml) and higher than those attained with a dose of 700 mg in HCV patients

(3361 ng\*hr/ml) where the  $\Sigma$  Free silymarinpeak concentrations ranged from 0.42 to 2.71 ug/ml. These data are reported in Appendix 1, Table 15 and Summary Tables 1 and 2. Therefore, a dose of 700 mg will likely result in  $\Sigma$  Free silymarin exposures for NAFLD subjects that will be higher than those observed with this dose in HCV subjects.

Since non-linear pharmacokinetics was observed at 560 mg, the highest dose evaluated in the Phase I study with NAFLD subjects, it is possible that there will be substantially higher  $\Sigma$  Free silymarin exposures and peak concentrations in this Phase II trial with a 700 mg dose than what was attained in the Phase I study for either HCV or NAFLD subjects. This possibility raises potential concerns for safety and tolerability since Flaig et al. (2007) found free silymarin flavonolignan concentrations above 10-12 ug/ml were associated with reversible grade 1 to grade 3 elevations in liver transaminase and unconjugated bilirubin concentrations in a Phase I study with a different formulation of two silymarin flavonolignans in patients with prostate cancer.

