### 4.3.1 Pharmacokinetic study

Specific goals of the study pharmacokinetic analysis will include 1) confirming estimates of PK parameters obtained during phase I, in which only a small number of NAFLD patients were enrolled, 2) a comparison with the HCV population, 3) identifying the sources and magnitude of intersubject pharmacokinetic variability on the basis of covariates, 4) observing changes in metabolite kinetics over time, and 5) potentially linking safety and outcome measures to pharmacokinetic profiles. The specific analyses are outlined below in section 6.4.

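### The exploratory exposure-response regression in section 6.4 names no baseline covariate, so its slope may reflect confounding rather than drug effect

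*Protocol*

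**What the plan says.** Section 6.4 has two steps. First, a population PK model is built, and backward elimination is used to examine the influence of participant characteristics, "including but not limited to weight, height, body surface area, body mass index, ALT, age, and gender on PK model parameters". Second, individual PK estimates from the final model "will be used to explore the relationship between various PK metrics and clinical outcomes"; in that logistic regression "the probability of positive (or negative) outcomes will be predicted based on various PK metric expressions (i.e. Cmax, AUC". Covariates are listed for the first step. For the second, only PK metrics are named.

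Four other places bear on this:
- Section 4.3.1 lists among the PK goals "identifying the sources and magnitude of intersubject pharmacokinetic variability on the basis of covariates" and, as a possibility, the linking of safety and outcome to PK.
- Section 2.3 names adherence as an explanatory variable in the exploratory exposure and response analyses.
- Dose Selection (section 1.0) says that summed silymarin concentration "is the best measure of silymarin exposure for assessment of safety and efficacy endpoints" and bases the dose choice on summed Total AUC. The paragraphs on non-linear PK that follow ask for Free concentrations to be considered separately.
- Section 6.2 makes the randomised three-arm chi-square test on the ITT set the main result. It uses no PK data.

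**The concern.** Participants are randomised to a dose, not to an AUC. Two people in the same arm can differ in exposure because of body size, liver function or adherence, and these may also bear on whether NAS falls by 2 points or enzymes rise. Section 6.4 makes the overlap concrete. If ALT or BMI survives backward elimination, each predicted AUC is partly a function of baseline ALT or BMI. Most active participants would be affected: the PK sub-study takes 10 per dose group, so 80 − 20 = 60 of the 80 on active drug contribute only single samples at visits, and their estimates lean more on the retained covariates.

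On the outcome side, section 1.0 says that BMI has correlated with NASH disease activity, and the secondary ALT/AST endpoint in section 2.3 is defined partly by the fall from the baseline value. A slope of outcome on AUC could then be read as an exposure effect, or as a toxicity threshold, when it only separates participants who differed at baseline. Section 6.2 says that the results are to guide the design of a phase III study.

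**Working it through.** The protocol gives no figure for this regression, so there is none to reproduce. The check asks how often an unadjusted slope is significant when the drug does nothing.

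**Inputs from the protocol.** 40 participants per arm, hence 80 on active drug (6.3); doses 420 and 700 mg (3.4); response 15% without drug effect (6.3, placebo arm).

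**Assumptions, not in the protocol.** SD of log exposure within dose, 0.5; correlation ρ between baseline severity S (standard normal) and log exposure within dose; odds ratio OR of response per SD of S.

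**Model.**
- log AUC = log(dose) + 0.5 × [ρS + √(1 − ρ²) × noise]
- logit P(response) = logit(0.15) + log(OR) × S, with no exposure term
- Logistic regression of response on log AUC, two-sided Wald test at 0.05

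**How much of the exposure variation is randomised.** The two doses differ by log(700/420) = 0.511 on the log scale. With equal arms, the between-dose variance is (0.511/2)² = 0.065, against 0.5² = 0.25 within dose. The randomised share is 0.065/0.315 = 21%. Under this assumed SD, about four fifths of the variation behind the slope is not randomised.

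**False-positive rate, unadjusted, 2,000 trials per setting.**

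| ρ | OR 1.5 | OR 2 | OR 3 |
|---|---|---|---|
| 0 | 4.2% | 5.0% | 4.4% |
| 0.2 | 5.0% | 6.2% | 8.0% |
| 0.4 | 6.7% | 11.4% | 20.4% |
| 0.6 | 10.6% | 17.8% | 39.2% |

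With OR 1 the rate is 4.0% to 4.8% at every ρ. Both links are needed, and the inflation is small when either is weak.

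**Further runs of the same design at other correlations.** About 4% at ρ 0.1, OR 2; 8% at 0.3, OR 2; 14% at 0.5, OR 2; 25% at 0.5, OR 3. Separate runs of the last setting gave 24% to 27%. The simulation standard error there is √(0.25 × 0.75/2,000), about 1 percentage point.

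**After adjustment.** With S in the model, the rate is 3.7% to 5.8% in every setting of the table's grid, and about 3% to 5% in the further runs even with five slopes fitted. Adjusting for dose arm alone does not help: at ρ 0.6, OR 3 the rate is 48.2%, against 39.2% unadjusted, because it removes the randomised part of the exposure contrast and leaves the confounded part.

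**Effect of the response rate.** At 47.5%, the protocol's figure for an effective drug, the same design gives about 10% (ρ 0.3, OR 2) and 22% (ρ 0.5, OR 2). The 15% rate is the one that fits a drug with no effect, so the lower figures are used here.

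**The case against.** The strongest reply is that this is an exploratory analysis whose covariates are normally settled in an analysis plan, which is not at hand. Section 6.4 says explore, section 4.3.1 makes the link to outcome only a potential goal, and section 2.3 already brings adherence into the analysis. Nothing says that the model is closed to other terms. This stands as a limit on the weight of the point. It does not remove it: the section does specify the regression, lists covariates for the step before, and names none here. Adherence does not stand in for severity.

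A reader might infer that the protocol expects liver disease and ALT to drive exposure, so that sicker participants' exposure and response will be linked. The documents do not support that:
- ALT is one of several candidates: "body mass index, ALT, age, and gender on PK model parameters will be investigated using a backward stepwise elimination procedure in NONMEM". No effect is predicted.
- The statement that "people with cirrhosis demonstrate pharmacokinetics which differ from people without cirrhosis" is given as a reason for excluding cirrhosis, so it concerns people not in the trial.
- The Free exposures in NAFLD that "were 4-fold greater than those for HCV patients" at 560 mg contrast two diseases; they show no gradient of severity within NASH. For Total exposure the contrast runs the other way, with NAFLD at about 60% of HCV.

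A reader might also count Cmax and AUC, Free and Total, over six isomers and their sum as 2 × 2 × 7 = 28 tests, with 28 × 0.05 = 1.4 false positives expected. The protocol names only Cmax and AUC and calls the metrics various; 28 is one possible count, not the plan. Nor does it say that this regression will set a phase III dose, or that placebo will enter as zero exposure.

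**Conclusion.** The point holds in conditional form. As written, section 6.4 names only PK metrics as predictors of outcome, and most of the exposure variation is likely to be non-randomised. If baseline severity or body size relates to both exposure and outcome, the unadjusted slope may reflect confounding. Under correlations of 0.1 to 0.5 and odds ratios of 1.5 to 3, at 15% response, the false-positive rate is about 4% to 25% instead of 5%; at the low end there is no problem at all. These sizes rest on the assumed correlation, odds ratio and log-exposure SD, none of which the protocol gives. The adjusted figures assume that the confounder is measured; baseline NAS, ALT and BMI are proxies and may leave some confounding behind. The consequence is confined to an exploratory analysis: the randomised efficacy comparison and its conclusions are untouched. The change is worth making because it is nearly free.

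**What to change.** Amend section 6.4, or the analysis plan it feeds, as follows:
- Fit the exposure-response regression in the two active arms.
- Include a short set of covariates already collected: baseline NAS, baseline ALT, weight or BMI, and the adherence measure of section 2.3. Dose arm alone is not a substitute.
- Take summed Total AUC and summed Free AUC as the main metrics, in line with Dose Selection, each in its own model. Present other metrics descriptively.
- Report the slope beside the randomised 700 versus 420 mg comparison and label it hypothesis-generating.

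No new data are needed. The cost is a few degrees of freedom. Expected responders on active drug number 80 × 0.15 = 12 if the drug does nothing and 80 × 0.475 = 38 at the protocol's assumed effect. One metric and four covariates make five slopes, that is 12/5 = 2.4 to 38/5 = 7.6 responders per slope. At the lower end estimates will be imprecise, so the list should stay short; if responders are few, the baseline value of the outcome being analysed is the covariate to keep first.

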## **6.5 Data Management**

Data will be submitted to the DCC via a distributed data entry system. The specifics of the system will be determined by the types and amount of data collected.

DCC personnel will closely monitor clinical center adherence to study protocol and data collection practices to ensure complete and accurate research data. Monitoring will be performed via established data management procedures with on-site monitoring visits conducted at designated intervals or as needed to facilitate the smooth conduct of the study. At the time of the on-site visit, Data Coordinating Center personnel will have access to all study and patient documents as well as availability of clinical center personnel. All patient and study documents will be kept highly confidential.

Data Coordinating Center personnel meet weekly to discuss study status, recruitment, compliance, review data issues or interim analyses, clinical center participation, and other issues that arise during the course of the study.

## **7.0 Study Organization**

### **7.1 Sites (See Table 1)**

This study will be conducted at four clinical centers within the United States. The clinical centers are all tertiary care institutions and academic medical centers with extensive experience in the conduct of clinical trials of antiviral agents for the treatment of chronic hepatitis C. A Data Coordinating Center will coordinate and oversee operations for the study, maintain the database and perform data analyses. This study will use the NIDDK repository. A central virology lab has yet to be selected.

### **7.3 Committees:**

A steering committee and an executive committee were formed to set policy and govern the conduct of the study.

**Steering Committee:** Serves as the primary governing body of the study; responsible for policy decisions; provides oversight in planning the overall study design, facilitates the conduct and monitoring of the study, and reporting study results; votes on and approves all major decisions, final protocol and subsequent amendments. Members consist of principal investigators of the clinical centers, the coordinating center, and the NCCAM and NIDDK project scientists. A chairperson is appointed by the NIH from among the clinical center PIs.

**Executive Committee:** Manages day-to-day issues of the study; makes decisions required between the Steering Committee meetings, as needed for efficient progress of the study, and reports its actions to the Steering Committee on a regular basis; organizes and sets agendas for Steering Committee meetings. Members consist of the Steering Committee chair, the Coordinating Center PI, and the NCCAM and NIDDK Project Scientists.

**7.4 Subcommittees:** Due to the small number of investigators and clinical sites involved in this study, all members will participate on ad hoc committees that will address issues that may arise during the course of the study including measurements, publications & presentations or ancillary studies. In addition, other subcommittees are as follows:

**Coordinators Subcommittee:** Attend to the day-to-day operations of the study including recruitment, protocol adherence, consistent and complete data collection at each clinical center. Make recommendations to the Steering Committee regarding any study issues that may require modification or resolution.

**Exemption Subcommittee:**, 2 hepatologists who are not recruiting participants into the study (Drs. [name] and [name], both of the National Institute of Diabetes and Digestive and Kidney Diseases) will review, on a case by case basis, protocol exemption petitions for subjects who do not meet one or more of the eligibility criteria (inclusion and exclusion) but are otherwise considered suitable candidates for enrollment. These exemptions will be considered only when they will not affect primary or secondary endpoints in the study. Examples might include liver biopsies or serological testing outside of predefined windows.

## **7.5 Data and Safety Monitoring Plan**

### **Introduction**

This phase II, randomized controlled trial aims to test the safety and efficacy of silymarin (Legalon®) in participants with NASH. The intervention poses greater than minimal risk to participants. Therefore, the data and safety monitoring plan (DSMP) for this study focuses on close monitoring by the principal investigators (PI) and prompt reporting of excessive adverse events and all serious adverse events to the National Center for Complementary and Alternative Medicine (NCCAM), the National Institute of Diabetes and Digestive and Kidney Diseases (NIDDK), the Data and Safety Monitoring Board (DSMB) and to the participating centers' IRBs.

The Data Coordinating Center (DCC) will monitor clinical center performance (e.g., recruitment, retention, data completeness, timeliness of data collection and submission) and protocol compliance. These reports, with summaries of adverse event data, will be provided to the DSMB for their quarterly reports and biannual calls or meetings, and to the Steering Committee at its annual meeting. DSMB reports will include both open and closed session reports, with only the latter including information by treatment arm.

Safety reports will be sent to the Principal Investigators and the NCCAM and NIDDK Project Officers. The Project Coordinator will be responsible for distributing these reports and assuring that all parties obtain copies of these reports.

The frequency of data review for this study differs according to the type of data and can be summarized in the following table:

| Data type                                                                                                       | Frequency of review                                                |
|------------------------------------------------------------------------------------------------------------------------|---------------------------------------------------------------------------|
| Recruitment
Retention
Protocol adherence(e.g., meeting
inclusion/exclusion criteria, treatment
compliance) | Quarterly reports for DSMB, NCCAM, and
NIDDK                           |
| Adverse events                                                                                                         | Quarterly reports for DSMB, NCCAM and
NIDDK                            |
| Serious Adverse Events (SAE)                                                                                           | As they occur for NCCAM, NIDDK, and
DSMB
Quarterly reports for DSMB |
| Laboratory data                                                                                                        | Yearly                                                                    |

